### Recruitment

Dissemination of recruitment information will be transmitted by facilities or institutions providing multiple services within a certain region, including sub-district offices, primary and secondary schools (for students’ grandparents), colleges for senior students, activity centres or day-care centres for older adults in the community, and community medical institutions. Contact details or addresses concerning these facilities or institutions will be obtained from the Chengdu Civil Affairs Bureau (cdmzj.chengdu.gov.cn), Chengdu Education Bureau (edu.chengdu.gov.cn), and Chengdu Health Committee (cdwjw.chengdu.gov.cn), and these units will be invited to disseminate recruitment information on- and offline. Interested older adults will be able to voluntarily enrol online. Eligible participants will receive electronic material concerning information necessary for participation, complete the online questionnaires, and upload their signatures, with participants able to contact the research team via phone to ask questions or to consult with them.

### Statistical methods

We will mainly follow the intention-to-treat principle. A per-protocol analysis will be conducted among those who complete 8 of 12 in-person video-link sessions and 16 of 24 home exercises, according to allocation.

For continuous data, quantile-quantile plots will be constructed to determine the standardised residuals and histograms with normal distribution curves. For descriptive statistics, continuous data with normal distributions, continuous data with non-normal distributions, and categorical data will be described using means ± standard deviations, medians (interquartile ranges), and frequencies, respectively. The significance level will be set at 0.05 for all analyses, and a two-sided 95% confidence interval will be used.

A generalised estimating equation (GEE) will be used to test the hypothesis comparing between-group differences in terms of effects on primary and secondary outcomes. Covariates and possible confounders will be adjusted, including sociodemographic variables, baseline values of the outcome variables, stratification factors (grade of Kellgren & Lawrence atlas), and non-comparable variables at baseline [74]. Additionally, we will identify other underlying predictors from the general KOA status and review treatments that accompany our intervention or follow-up, which will be selected (*p* < 0.2) according to a univariate analysis using a backward stepwise procedure. Furthermore, for ordinal categorical secondary outcomes, we will fit the GEE using an alternating logistic regression model, assuming an exchangeable correlation structure, adjusted for all the predictors, and with final results reported as odds ratios. Given a close relation to the quasi-likelihood resolution of GEE [75], maximum likelihood estimation will be used to impute missing data.

To test the hypothesis concerning the mechanisms associated with the effects on pain and function, a cross-lagged model fitted within the structural equation modelling (SEM) will be used. SEM is an approach that allows simultaneous modelling of several variables and enables an investigation of more complex mediation models [76–78]. The variables of interest as mediators in the relationship between effects on pain/function and irritability are changes in outcomes on mental health and on social participation/support, which will be studied using two separate four-wave cross-lagged path models (during the intervention and follow-up). The time lag between each measurement will be 4 weeks. In addition to estimating cross-lagged effects, the specified model will include correlations within time points, autoregressive effects (stability), and underlying predictors, similar to the process of GEE analysis [79]. Moreover, full-information maximum likelihood will be used to handle missing data and estimate covariance matrices [80]. Additionally, data from both groups will be included in the cross-lagged model coded as two classified labels.

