**Methods:**

In this proposed two-parallel group (neuromuscular exercise versus quadriceps exercise), single-blinded, randomised controlled trial, participants aged ≥50 years with osteoarthritic knee pain will undergo a 12-week intervention, comprising video-linked education, supervised exercises, and a 12-week follow-up. Seven measurements will be taken to collect longitudinal data. A generalised estimating equation will be used to establish the adjusted difference in effectiveness on pain, function, irritability, and psychosocial outcomes between participants undertaking neuromuscular exercises and those undertaking quadriceps exercises. The primary outcomes are overall average pain in the knee joint during walking, as assessed through the 11-point Numerical Pain Rating Scale, and the Western Ontario and McMaster Universities osteoarthritis index physical function subscale. Furthermore, pressure pain threshold and changes in self-report pain scores pre-, during, and post-exercise were also measured as an indication of irritability. In addition, both the 6-min walk test and a timed up & go test were used to assess walking function performance. Finally, patients’ emotions (e.g., fear and catastrophising), self-trust, needs in terms of disease knowledge, mental resilience, social support and health-related quality of life were investigated. Two four-wave cross-lagged models will be used to investigate directional relationships, aiming to investigate the complex mechanisms concerning the effects of exercise programmes.

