### Objective

This clinical trial will investigate effects on pain, function, mental health, social participation/support, and health-related quality of life for community-dwelling older participants with KOA through a 12-week program that combines progressive exercise and systematic education under the video-linked instruction of a physiotherapist and with the support of a participant’s family. The key mechanisms of irritability, physiological outcomes, mental health, and social participation/support will be further explored. We hypothesised that: (i) progressive exercise and systematic education will benefit participants with KOA, and that neuromuscular exercise will have a better effect than quadriceps exercise; (ii) pain relief benefits from a decrease in peripheral hyperalgesia after a period of regular exercise training, which is mediated through the improvement of mental health and social participation/support, and; (iii) after a period of regular exercise training, a decrease in exercise-related irritability will enhance functional improvement, which is mediated through improvement in mental health and social participation/support.

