### Primary outcomes

Primary outcomes are as follows: (i) overall average pain in the knee joint during walking over the previous month: an 11-point NPRS will be used to investigate participant-reported pain ranging from 0 (no pain) to 10 (the worst pain), with 1.8 units having been reported as a minimum clinically important difference (MCID) [54]; and (ii) difficulty with physical function: the Western Ontario and McMaster Universities osteoarthritis index (WOMAC) physical function subscale [55] will be used to evaluate self-reported dysfunction using 17 questions. Total subscale scores will range from 0 to 68, with higher scores indicating more serious dysfunction. An MCID in terms of physical function in KOA has been determined as six units [56].

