### Sample size

PASS 15.0 (East Kaysville, USA) software will be used to test for two means in a repeated measures design, based on linear-mixed effect models [70–72], with estimations of the correlation coefficient between different observations made on the same participant set at 0.6 [9]. The sample size required will be sufficient to show a moderate effect size, that is, a 0.5 standard deviation in the between-group difference in relation to the primary outcomes (knee pain during walking and WOMAC function). With a yielding power of 80% and a significance level of 0.05, the sample size is intended to comprise 44 participants in each group. With allowance for a dropout rate of 20%, each group requires 55 enrolled participants.

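### Two primary outcomes are each tested at 0.05 with no rule on whether one or both must succeed; if either suffices, the false-claim rate is about 7–10%, and if both are needed, power is about 64–73%

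*Protocol article*

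**What the plan says.** The abstract, Table 1 and the Primary outcomes section all name two primary outcomes. The first is "overall average pain in the knee joint during walking over the previous month", on the 11-point NPRS; the second is the WOMAC physical function subscale.

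Hypothesis (i) in the Objective section is a single statement that "neuromuscular exercise will have a better effect than quadriceps exercise". It is not tied to one outcome or to both.

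In Statistical methods, a generalised estimating equation "will be used to test the hypothesis comparing between-group differences in terms of effects on primary and secondary outcomes". The same section fixes the level: "The significance level will be set at 0.05 for all analyses, and a two-sided 95% confidence interval will be used".

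The Sample size section aims to detect "a 0.5 standard deviation in the between-group difference in relation to the primary outcomes (knee pain during walking and WOMAC function"), with 80% power, a significance level of 0.05 and a within-participant correlation of 0.6. This gives 44 per group, or 55 after 20% dropout.

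The article does not require both outcomes to succeed, does not order them and does not divide the 0.05 between them.

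**The concern.** With two primary outcomes, the trial's error rate and its power both depend on what counts as success. Read as written, either outcome at p<0.05 can be presented as support for hypothesis (i), and two chances at 0.05 give more than 5% error overall. If the team means that both must succeed, error is held, but the chance of success is below the 80% that a reader takes from the sample-size section.

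Either way, the planning figures (5% error, 80% power) do not both describe the trial's main conclusion. A rule chosen after the results are known would not be credible, and 71 participants had already been enrolled by April 2021 (Study status).

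**Working it through.** **Inputs from the protocol article.** Two primary outcomes; 0.05 for all analyses, with two-sided intervals; effect 0.5 SD; power 80%; within-participant correlation 0.6; 44 per group; dropout 20%; 1:1 allocation.

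**Assumptions, not in the article.**
- One between-group test per outcome.
- Test statistics for pain and function that are bivariate normal with correlation r. The article's 0.6 concerns repeated observations on one participant, not pain against function, so r is varied.
- Four measurements in the sample-size formula. The article does not state the number; four is inferred because it returns 44.

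**1. Reproduce the stated size.** Under compound symmetry with m measurements, n per group = 2 × ((1.960 + 0.842)/0.5)² × (1 + (m − 1) × 0.6)/m.
- m = 1: 62.8, so 63.
- m = 4: 62.79 × 0.70 = 43.95, so 44. Power at 44 is 80.0%.
- m = 6 or 7: 42.
- Dropout: 44/(1 − 0.20) = 55.

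The stated 44 and 55 are reproduced, at the full two-sided 0.05 for a single outcome.

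**2. Error if a win on either outcome counts.** With no true difference on either, error = 1 − P(|Z₁| < 1.96 and |Z₂| < 1.96). At r = 0 this is 1 − 0.95² = 9.75%. The one-direction column is 1 − P(Z₁ < 1.96 and Z₂ < 1.96), a false claim for neuromuscular exercise.

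| r | Any false claim | False claim for neuromuscular |
|---|---|---|
| 0 | 9.75% | 4.9% |
| 0.5 | 9.1% | 4.5% |
| 0.7 | 8.35% | 4.2% |
| 0.8 | 7.8% | 3.9% |
| 0.9 | 7.0% | 3.5% |

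The benchmarks are 5% for the first column and 2.5% for the second.

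**3. Power if both outcomes are required.** With 44 per group and a variance factor of 0.70, the expected test statistic is 0.5/√(2 × 0.70/44) = 2.80. With a true 0.5 SD effect on both outcomes, the probability that both exceed 1.96 is 64% at r = 0, 69% at r = 0.5 and 73% at r = 0.8.

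**4. Power under control of family-wise error.**
- A fixed 0.025 per outcome (critical value 2.241): Φ(2.803 − 2.241) = 71.3% per outcome. Restoring 80% would need 54 per group, or 54/0.8 = 67.5, so 68 enrolled.
- Hochberg (both significant if both p<0.05; otherwise only the smaller, and only if p<0.025), same effects:

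| r | Power per outcome | Power for at least one |
|---|---|---|
| 0.5 | 77.6% | 86.3% |
| 0.7 | 77.3% | 83.3% |
| 0.8 | 77.3% | 81.6% |

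With no true effect on either, the same model gives a Hochberg family-wise error of 5.0% at r = 0, 4.8% at 0.5 and 4.4% at 0.8.

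**The case against.** The strongest objection is that the inflation is conditional. The article never says that one win is enough. Hypothesis (i) is a single statement, and both outcomes are named side by side, so a both-required reading is possible. A reader might infer that the false-positive rate simply is 8–10%. The text does not support that: the figure needs the either-outcome rule and an assumed correlation, and it falls to 7.0% at r = 0.9. This part of the objection stands. It does not remove the problem, because the both-required reading lowers power instead.

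Second, hypothesis (i) is directional, and the 7–10% counts false claims for quadriceps exercise as well. This also stands: a false claim for neuromuscular exercise alone is about 3.5–4.9%. That is still above the 2.5% that one two-sided 0.05 test allows in one direction.

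Third, multiplicity procedures are commonly left to the analysis plan, and an article is condensed. That would answer mere silence. Here the article fixes 0.05 for all analyses and builds the sample size on it, so a later plan that divided the 0.05 would contradict this text and change the basis of the stated power.

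A reader might also infer that the sample size is miscalculated or that the trial must be enlarged. Neither follows. The figures 44 and 55 reproduce; they simply answer a per-outcome question.

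**Conclusion.** The point holds in conditional form. The article gives two primary outcomes the full two-sided 0.05 each and leaves the success rule open.

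- **Either outcome suffices:** two-sided family-wise error is about 7–10% for r between 0.9 and 0, roughly half of it in favour of neuromuscular exercise.
- **Both required:** error is controlled, but power to win both at 44 per group is about 64–73% for r between 0 and 0.8.

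Under neither rule does the trial have both 5% error and the stated 80% power for its main conclusion; the 80% is per outcome. These results rest on an assumed pain–function correlation and one test per outcome. The power figures also need a true 0.5 SD effect on both outcomes and the inferred four measurements. Table 1 lists all seven assessments as time points of primary interest, so separate tests by visit would raise the error further.

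**What to change.** Before unblinding, add to Statistical methods: *The two primary outcomes are tested by the Hochberg procedure at family-wise two-sided 0.05. Both are significant if both p<0.05; otherwise only the outcome with the smaller p-value is significant, and only if that p<0.025.* Limit the statement on 0.05 for all analyses to match.

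Do not name Holm with this wording. Under Holm the smaller p-value must first pass 0.025, so p = 0.03 and p = 0.04 would reject neither hypothesis, whereas Hochberg rejects both.

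In the Sample size section, restate power at 44 per group with 0.5 SD on both outcomes: about 77–78% per outcome and about 82–86% for at least one under Hochberg (r = 0.5 to 0.8, stated as an assumption). Give 71% per outcome at 0.025 as the conservative figure. State the number of measurements used; four is only inferred.

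If the team intends that both outcomes must succeed, say so instead and report the 64–73%.

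The cost is two short text changes and a per-outcome power a little under 80%. No extra participants are needed; 68 enrolled per group would be required only to keep 80% per outcome at a fixed 0.025.

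### The primary GEE adjusts for an open-ended, data-selected covariate set on 88 to 110 participants; with the usual uncorrected sandwich variance the 5% test would run at about 6 to 10%

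*Protocol article*

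**What the plan says.** The Statistical methods section of the protocol article fixes three things.

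- **The test.** "A generalised estimating equation (GEE) will be used to test the hypothesis comparing between-group differences" on primary and secondary outcomes. "The significance level will be set at 0.05 for all analyses", and "a two-sided 95% confidence interval will be used".
- **The adjustment.** "Covariates and possible confounders will be adjusted, including sociodemographic variables, baseline values of the outcome variables". The list continues with Kellgren & Lawrence grade and any variable on which the arms turn out not to be comparable at baseline. Further predictors, drawn from general knee osteoarthritis status and accompanying treatments, are admitted by univariate screening at p < 0.2 with a backward stepwise procedure.
- **The size.** In the Sample size section, "the sample size is intended to comprise 44 participants in each group", that is 88 in all. Allowing for 20% dropout, 55 per group (110) are enrolled.

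For the primary outcomes the article does not name the variance estimator, the reference distribution or any small-sample correction. It does not say how many covariates will enter.

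**The concern.** GEE inference customarily rests on the sandwich variance with a normal reference. That variance is biased downward in finite samples. The bias depends on the number of participant-level parameters relative to the number of participants, not on the number of participants alone. Eighty-eight to 110 participants looks comfortable for a two-arm comparison with few covariates, but less so when the model may absorb ten to twenty covariate columns, some chosen after seeing the data.

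The Objective section hypothesises that neuromuscular exercise is better than quadriceps exercise. If the standard errors are too small, intervals for both primary outcomes are too narrow, and a difference between two active programmes is declared more often than the stated level allows.

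**Working it through.** **Inputs from the article.** Two-sided 0.05; "With a yielding power of 80% and a significance level of 0.05"; "a 0.5 standard deviation in the between-group difference in relation to the primary outcomes"; "correlation coefficient between different observations made on the same participant set at 0.6"; 44 per group evaluable and 55 enrolled; 1:1 allocation; seven assessments, so six after baseline.

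**Assumptions (not in the article).** Uncorrected sandwich with a normal reference; number of covariate columns p between 0 and 25; normal outcomes; complete data; no true effect; one arm effect common to all visits.

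**Step 1. Reproduce the sample size.** n per group = 2(1.960 + 0.842)² / 0.5² × [1 + (m − 1) × 0.6] / m = 62.79 × [1 + (m − 1) × 0.6] / m.

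- m = 4: 62.79 × 0.70 = 43.95, so 44, the stated figure.
- m = 6 or 7: 41.86 or 41.26, so 42.
- Dropout: 44 / 0.80 = 55, as stated.

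The sample size stands. It makes no allowance for covariate degrees of freedom.

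**Step 2. Analytic approximation.** With covariates constant over visits, the uncorrected variance is shrunk by about 1 − q/N, where q = p + 2 (intercept, arm, covariates). The nominal 1.96 then acts as 1.96 × √(1 − q/N) on a t distribution with N − q degrees of freedom. Example: N = 88, p = 15, q = 17 gives 1.96 × √(71/88) = 1.96 × 0.898 = 1.76, and the two-sided tail of t on 71 degrees of freedom is 8.3%.

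**Step 3. Simulation.** 6,000 runs per cell; six visits; exchangeable correlation 0.6, also used as the working correlation; visit effects; mixed binary and continuous covariates. Monte Carlo standard error is about 0.3 to 0.4 points. Type I error in %:

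| Covariate columns p | N = 88, uncorrected | N = 88, analytic | N = 88, corrected | N = 110, uncorrected | N = 110, analytic | N = 110, corrected |
|---|---|---|---|---|---|---|
| 0 | 5.8 | 5.6 | 5.0 | 5.7 | 5.5 | 5.1 |
| 4 | 6.0 | 6.2 | 4.9 | 5.9 | 5.9 | 5.1 |
| 8 | 6.8 | 6.9 | 5.0 | 7.2 | 6.5 | 5.6 |
| 12 | 8.4 | 7.6 | 5.4 | 7.3 | 7.0 | 5.4 |
| 15 | 9.1 | 8.3 | 5.7 | 7.4 | 7.5 | 4.9 |
| 20 | 9.8 | 9.4 | 5.2 | 9.1 | 8.3 | 5.6 |
| 25 | 11.9 | 10.8 | 5.5 | 9.7 | 9.2 | 5.4 |

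Corrected here means the sandwich scaled by N/(N − q), with a t reference on N − q. A separate simulation on participant means (8,000 runs per cell; 5, 10, 15 and 20 columns) gave 5.9, 8.1, 9.0 and 10.1% at N = 88, and 6.1, 6.9, 8.0 and 8.5% at N = 110.

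**Step 4. Mimic the selection rule.** If Kellgren & Lawrence grade (0 to III at entry) is treated as categorical, one baseline value + 3 for grade + two sociodemographic variables = 6 degrees of freedom before any data-driven addition. Pure-noise candidates were then added if unbalanced at p < 0.05 (an assumed threshold), or if they passed p < 0.2 and backward elimination:

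| Starting set and candidates | Mean df at N = 88 | N = 88 | N = 110 |
|---|---|---|---|
| Six df, no additions | 6 | 6.7% | 6.2% |
| 2 sociodemographic, 10 candidates | 7.8 | 7.8% | 7.0% |
| 5 sociodemographic, 10 candidates | 10.8 | 8.4% | 7.5% |
| 5 sociodemographic, 20 candidates | 12.5 | 9.0% | 8.0% |

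The Kauermann-Carroll variance with a t reference gave 5.0 to 5.8% throughout.

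**The case against.** The strongest reply is that both drivers are supplied by the reader. The article never says the sandwich is uncorrected, and the choice of GEE variance estimator is routine detail for a statistical analysis plan, which is not shown here. The covariate count is also unknown: the sociodemographic variables could be two columns or ten, and Kellgren & Lawrence grade could enter as a linear score. With 0 to 4 columns the rate is only about 6%. The number of participants may also be nearer 110 than 88, because the analysis mainly follows intention to treat and intends to handle missing data, so people with partial follow-up may contribute. At 110 the inflation is smaller.

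Most of this stands. A reader might infer that the trial's 5% level is in fact 7 to 10%, or that its intervals are known to be too narrow. The article does not support that, because it commits to no estimator that would make it so. Nor is silence on the estimator an error in itself.

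What the reply does not remove is the adjustment rule. Imbalance-triggered and p < 0.2 selection are written into the article, and they let the number of parameters grow after the data are seen. That rule determines how far the level drifts under the customary default.

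**Conclusion.** The point holds as a conditional one of modest size. Under an uncorrected sandwich with a normal reference, the type I error is about 6% with 4 to 6 covariate degrees of freedom, about 7 to 8% with 10 to 15 (up to 9.1% at N = 88 with 15), and about 8 to 10% with 20. The excess over nominal is therefore roughly 1 to 5 percentage points for each primary outcome. It rests on the assumptions listed above; missing data, non-normal scores and arm-by-visit terms were not examined. The estimator and the count may yet be settled favourably in an analysis plan. The selection rule that leaves the count open is stated now and should be changed.

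**What to change.** In the primary model, replace the imbalance-triggered and p < 0.2 selection with a short list fixed before unblinding: the baseline value of the outcome, the stratification factors (sex and Kellgren & Lawrence grade, as in the section on participant assignment) and a few named sociodemographic variables. Data-selected models can be kept as labelled sensitivity analyses.

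Add one sentence: GEE tests and intervals use a small-sample-corrected sandwich variance (for example Kauermann-Carroll) with a t reference on participants minus parameters. Name the correction, because they differ: Mancl-DeRouen with a t reference gave 2.3 to 4.9% in the Step 3 simulation and was conservative with many covariates.

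The cost is wider intervals. The width ratio is (t / 1.96) / √(1 − q/N):

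- 5 columns, N = 110: (1.983 / 1.960) × √(110/103) = 1.012 × 1.033 = 1.05.
- 20 columns, N = 88: (1.997 / 1.960) × √(88/66) = 1.019 × 1.155 = 1.18.

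Intervals are thus 5 to 18% wider than uncorrected ones, and a short list keeps the increase near the lower end. No participants, visits or measurements change.

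### The missing-data rule for the primary GEE rests on a likelihood that GEE does not have; read literally as a single fill-in, it makes standard errors too small at the planned 20% dropout

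*Protocol article*

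**What the plan says.** The Statistical methods section makes GEE the confirmatory analysis: "A generalised estimating equation (GEE) will be used to test the hypothesis comparing between-group differences in terms of effects on primary and secondary outcomes". Missing data are covered in the same paragraph. The reason given is "Given a close relation to the quasi-likelihood resolution of GEE", and the rule is "maximum likelihood estimation will be used to impute missing data". The section names no missingness assumption for this analysis. It states a working correlation only for another part of the analysis: "for ordinal categorical secondary outcomes, we will fit the GEE using an alternating logistic regression model, assuming an exchangeable correlation structure".

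Two other places bear on the point. For the cross-lagged structural equation models, the same section says that "full-information maximum likelihood will be used to handle missing data and estimate covariance matrices". The Sample size section describes a "test for two means in a repeated measures design, based on linear-mixed effect models", with "estimations of the correlation coefficient between different observations made on the same participant set at 0.6", and raises 44 evaluable participants per group to 55 enrolled for 20% dropout.

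**The concern.** The rule is stated together with its reason, and the reason is wrong. Quasi-likelihood specifies a mean and a variance function. GEE adds a working correlation and solves estimating equations, and no joint distribution of the repeated scores is specified. GEE therefore contains nothing from which maximum likelihood could handle a missing score. Maximum likelihood also estimates parameters; it does not by itself impute values. The structural equation models do have a likelihood, so full-information maximum likelihood is coherent there. That reasoning does not carry over to the GEE.

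The nearest literal procedure fits a likelihood model (for example by EM), replaces each missing score by its expected value, and runs the GEE on the completed data. The GEE then counts predictions as observations. Both primary outcomes, walking pain and WOMAC function, are affected. The plan itself expects 20% dropout, so the rule will be used.

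**Working it through.** **1. The plan's own figure.** Inputs from the Sample size section: difference 0.5 SD, correlation 0.6, power 80%, level 0.05 (taken as two-sided). The number of repeated measures is not stated; four (baseline and weeks 4, 8 and 12) is an assumption.

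- Variance of a four-measure average: (1 + 3 × 0.6)/4 = 0.70.
- n per group = 2 × (1.960 + 0.842)² × 0.70/0.5² = 43.95, so 44.
- 44/(1 − 0.20) = 55.

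Both figures are reproduced, and nothing below changes them.

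**2. Single fill-in, last-visit contrast, closed form.** Assumptions: outcome SD 1, equal correlation 0.6 between visits, 55 per arm, adjustment for baseline, and a fraction m = 0.20 missing at random chance.

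- Residual variance after baseline: 1 − 0.6² = 0.64. The complete-data variance of the arm difference is 2 × 0.64/55 = 0.02327.
- Partial correlation of two later visits given baseline: (0.6 − 0.36)/0.64 = 0.375.
- Let R² be the share of residual variance that the observed later visits predict. It is 0 if none was observed, 0.375² = 0.141 with week 4, and 2 × 0.375²/1.375 = 0.205 with weeks 4 and 8.
- Reported variance ≈ 0.02327 × [(1 − m) + m·R²].
- True variance ≈ 0.02327 × [(1 − R²)/(1 − m) + R²].
- Type I error ≈ 2 × [1 − Φ(1.96 × reported SE/true SE)].

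| Visits used to impute | Reported SE | True SE | Ratio | Type I error |
|---|---|---|---|---|
| baseline only | 0.136 | 0.171 | 0.80 | 11.7% |
| baseline, week 4 | 0.139 | 0.168 | 0.83 | 10.6% |
| baseline, weeks 4 and 8 | 0.140 | 0.167 | 0.84 | 10.1% |

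A simulation of the second row (6,000 replicates) gave SE 0.139 against 0.169 and a type I error of 10.7%. At 10% and 30% missing it gave 7% and 15%.

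**3. Single fill-in, simulated with robust GEE standard errors.** With 20% random dropout there was no bias. The last-visit SE ratio was about 0.80, with a type I error of about 12%. For the visit-averaged effect the ratio was 0.88 to 0.92, with 7.5% to 8%. A separate run of 2,500 replicates gave 7.8% with three post-baseline visits and 6.6% with six for the averaged effect, and 12.1% and 10.7% for the last visit. Robust standard errors at this sample size account for a little of the excess: with complete data, type I error was 6.2% in the step 4 simulation.

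**4. Dropout depending on the previous score.** The mechanism is deliberately severe: dropout depends on the last score in opposite directions in the two arms. True effect zero, last-visit contrast, 1,000 replicates. CS is equal correlation 0.6; AR(1) is 0.8 between neighbouring visits.

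| Method | Bias (SD), about 20% dropout: CS; AR(1) | SE ratio: CS; AR(1) | Type I error: CS; AR(1) |
|---|---|---|---|
| Single fill-in, then GEE | +0.01; +0.01 | 0.76; 0.78 | 14.9%; 12.7% |
| Unimputed GEE, independence | −0.07; −0.11 | 0.95; 0.94 | 9.4%; 11.9% |
| Unimputed GEE, exchangeable | 0.00; −0.02 | 0.96; 0.95 | 6.4%; 6.8% |
| Likelihood mixed model | +0.01; +0.01 | 0.95; 0.95 | 6.5%; 6.5% |
| Complete data | +0.01; +0.01 | 0.95; 0.95 | 6.2%; 6.2% |

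At 35% dropout under CS, the single fill-in reaches a type I error of 23.0%, still without bias. The independence GEE has bias −0.13 SD. Monte Carlo error on type I error is about 0.7 to 1.3 percentage points.

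The fill-in keeps the estimate and understates its error. The unimputed GEE keeps the error about right and may shift the estimate, by an amount that depends on the working correlation.

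**The case against.** The article does not say that imputation is single. Multiple imputation from a likelihood-fitted model is not excluded, and the number of imputations and the variance rule are details that an analysis plan or full protocol commonly holds. This stands as far as it goes: the single fill-in is the literal reading, not a certainty. It does not rescue the stated rationale, which is an error on the page. A fuller document that built on it would inherit it.

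The inflation also depends on the contrast. The protocol names no single primary visit, and its sample size is reproduced by a time-averaged variance. For that contrast type I error is about 7% to 8%. This stands too, and is why both contrasts are given.

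A reader might infer that the primary comparison both loses validity under missing at random and gets standard errors that are too small. The documents and the calculations do not support that. A larger bias, 0.12 SD at week 24, can be produced, but only by a GEE without imputation, with an independence working correlation that the protocol never states, about 25% dropout and opposite mechanisms by arm. With exchangeable correlation the same set-up gives about 0.05 SD.

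A reader might also infer that sizing on a mixed model and analysing by GEE is itself an error. It is not: for a continuous outcome the two can target the same mean contrast, and this pairing is ordinary practice.

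**Conclusion.** The point holds in a limited form. The quasi-likelihood rationale is wrong. On its literal reading the rule makes confidence intervals for both primary outcomes too narrow at the sponsor's own dropout rate, with type I error of about 12% for a last-visit contrast and about 7% to 8% for a visit-averaged one. The arm difference remains about unbiased, provided that data are missing at random and the imputation model is right.

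If nothing is imputed, the risk is bias. It is near zero under a correct exchangeable working correlation and larger under independence: 0.07 SD at about 20% dropout, which is 0.07/0.5 = 14% of the design difference, under a deliberately severe mechanism. The text does not settle which reading will be carried out.

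The sizes rest on 55 per arm, correlation 0.6, baseline adjustment and the assumed dropout patterns.

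**What to change.** Delete the quasi-likelihood rationale and replace the missing-data sentence for the GEE with one of the following, stating in either case that data are assumed missing at random:

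- **Keep GEE as primary.** Missing primary-outcome scores are multiply imputed separately by arm, with baseline and all earlier scores in the imputation model and at least 20 imputations. The GEE is fitted to each completed data set and the results are combined by Rubin's rules.
- **Use a mixed model as primary.** Primary outcomes are analysed by a likelihood-based mixed model for repeated measures on all observed data without imputation, in line with the model used for the sample size.

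Either option removes the understated standard errors. The choice should be fixed before outcomes are seen by arm.

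The cost is a change of wording: no new data and no new participants, with 44 and 55 per group unchanged. Intervals will be wider than a single fill-in would report, by 1/0.92 to 1/0.88, or about 9% to 14%, for the visit-averaged effect, and by 1/0.80, or about 25%, for the last visit. The extra width is uncertainty that the fill-in would have hidden.
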